## Abstract

**Background:**

Invasive treatment (coronary angiography and intervention if feasible) of patients with acute coronary syndrome (ACS) has been shown to lead to better outcomes than medical therapy alone, but the elderly have been under-represented in many of the studies. In the elderly, medical therapy is common in ACS. Fear of complications related to the procedure and unclear benefit in older patients are common reasons for invasive procedures being withheld. Our hypothesis is that invasive treatment of elderly patients with ACS will lead to a better outcome in terms of survival and quality of life than medical therapy alone, with acceptable risk.

**Methods/Design:**

This multicenter, randomized controlled trial of patients 80 years of age and over has two parallel treatment arms, a medical group and an invasive group. In Swedish hospitals, 200 patients with non-ST elevation myocardial infarction or unstable angina will be randomized to medical or invasive treatment strategy. The primary outcome measure is the combined endpoint major adverse cardiac or cerebrovascular event (MACCE) within one year. Secondary outcome measures include quality of life, angina, and adverse events such as bleeding. Assessments will be conducted during hospitalization, at 1 month after allocation, and at 12 months.

**Discussion:**

This study seeks to determine the efficacy and safety of invasive and medical treatment strategies in the elderly with ACS. The study is currently recruiting.

**Trial registration:**

ClinicalTrials.gov trial identifier: NCT02126202. Registered on 7 January 2014.

## Background

In acute coronary syndrome (ACS), large randomized studies have shown a survival benefit of invasive treatment strategy over medical therapy [1, 2]. Under-representation in clinical trials and possibly fear of complications in older patients has led to a suspected under-utilization of invasive treatment in the elderly compared to that in younger population groups. However, a substudy from a large randomized trial [3] showed that the oldest patients appeared to benefit the most. In 2007, the American Heart Association published a statement [4] in order to highlight the problem. In contrast, a recent trial [5] failed to confirm survival benefit in elderly patients with non-ST elevation myocardial infarction ACS unless cardiac enzyme levels were substantially elevated.

### Study objectives and hypothesis

This randomized controlled trial (RCT) aims to address a fundamental question: which treatment strategy in elderly patients with myocardial infarction results in a better outcome with acceptable risk? Specifically, which treatment strategy improves survival and results in less morbidity and better quality of life? Equally important are the adverse events associated with each treatment strategy.

We hypothesize that revascularization in elderly patients with ACS will lead to gain in terms of outcome and quality of life compared to medical therapy alone. Secondly, we hypothesize that adverse events will occur, but will be within an acceptable range.

## Methods/Design

### Design of trial

The octogenarians study is an academically sponsored and principal investigator-initiated study. The study design adheres to the ‘CONsolidated Standards of Reporting Trials’ (CONSORT) statement [6].

The study is a phase 4 RCT with two parallel treatment arms: invasive therapy and medical therapy. Invasive therapy will include a coronary angiography and, if feasible, revascularization with percutaneous coronary intervention (PCI) or coronary artery bypass grafting (CABG). Blinding of study participants is not possible due to the invasive treatment arm, which makes the trial an open-label trial.

### Participants and recruitment

The trial is a multicenter study. Participants will be recruited from different sites in the southern and southwestern parts of Sweden. The hospitals participating are Sahlgrenska University Hospital in Gothenburg, Norra Älvborg Regional Hospital in Trollhättan, Skåne University Hospital in Lund, and Skaraborg Hospital in Skövde.

Participants will be identified by the treating physicians at these hospitals. Patients who meet the inclusion criteria will be approached by a physician who will provide a brief summary of the study. If the patient is interested in taking part, he or she will be asked to provide written informed consent. The inclusion criteria are: equal or greater than 80 years of age; ACS with ischemic symptoms (mainly chest pain) lasting over 10 minutes within the previous 72 hours, and ischemic ST-segment depression ≥ 1 mm and/or elevated troponin I, troponin T, or CK-MB; and written informed consent provided before randomization.

The exclusion criteria are: PCI within 30 days prior to randomization; suspected ongoing active internal bleeding; ST-segment elevation of ≥ 1 mm in two contiguous leads on ECG (electrocardiogram) enrollment in another study that has not completed the follow-up phase; known allergy to aspirin or P2Y_12_ antagonists; severe dementia; expected limited 1-year survival due to another disease(s); and unwillingness to participate in the trial or expected problems with compliance. Patients who meet the inclusion criteria but who are not able to participate for various reasons will be registered in a trial screening log.

### Ethics and procedure

The ethical aspects of this study have been approved by the Ethical Review Board in Gothenburg (Diarie number 157–09). The project will be conducted according to the World Medical Association Declaration of Helsinki [7].

### Randomization

The age of participants (between 80 and 84-years-old or ≥85-years-old) will be used to determine the subgroup for random allocation. This stratification is due to the possibility of unbalanced treatment arms regarding age. The random assignment to one of the two treatment arms will be conducted independently of the project staff by using sequentially numbered and sealed opaque envelopes. The envelopes will contain the group allocation on a written insert, based on a predetermined random computer-generated sequence.

### Crossover

Efforts should be made to keep the initial treatment allocation, but a certain crossover rate can be expected. Patients randomized to the invasive treatment group will receive medical treatment in case of coronary anatomy unsuitable for intervention. Patients in the medical treatment group will undergo coronary angiography with possible revascularization in case of ischemia leading to refractory chest pain, hemodynamic instability (including cardiogenic chock), heart failure, or life-threatening cardiac arrhythmias.

### Intervention procedures

*Invasive treatment (intervention arm of the RCT)*: coronary angiography will be performed with the use of 5 to 8 F catheters via the femoral or radial approach at the operator’s discretion. Revascularization with PCI or CABG will be performed if feasible and if acceptable to the patient. For all patients, standard medication (as mentioned below) will be administered if the patient has no contraindications. If PCI is performed, the patients will be treated with heparin or bivalirudin according to local guidelines and at the operator's discretion. *Medical treatment (control arm of the RCT)*: patients randomized to medical treatment will receive optimized medical treatment and will not undergo a coronary angiography.

### Trial medication

The following medication is recommended but not mandatory in both treatment arms.

Aspirin will be administered to all patients on a daily basis in a maintenance dose of between 75 and 160 mg. If the patient is previously untreated with aspirin, a loading dose of between 160 and 320 mg will be given.

Other antiplatelet medications include clopidogrel (with a loading dose of between 300 and 600 mg) or ticagrelor (loading dose of 180 mg) will be administered as soon as possible, and always before the coronary angiography, in patients randomized to invasive treatment.

Treatment with a statin (such as atorvastatin) will be started as soon as possible. Beta-blockers are often included as an anti-ischemic treatment in the absence of contraindications. Long-term treatment is recommended in the case of reduced left ventricular function. Nitroglycerin (intravenous, oral, sublingual or buccal) is recommended for symptom relief if necessary. ACE inhibitors are indicated long-term in all patients with heart failure (left ventricular ejection fraction ≤40%) and in patients with diabetes mellitus or hypertension.

### Definitions

Blood samples for hemoglobin will be obtained at baseline, and if there is suspicion of bleeding. Blood samples for platelet count will be obtained at baseline and if there is suspicion of bleeding. Blood samples for potassium, sodium, and creatinine will be obtained at baseline. Blood samples for CK-MB (creatine kinase-MB) and/or Troponin Tor Troponin I will be obtained at baseline, and if there are symptoms of myocardial ischemia. All-cause mortality will be analyzed for this study. For the purposes of this study ST-elevation myocardial infarction (STEMI) will be defined as chest pain lasting more than 10 minutes in combination with ST-segment elevation (more than 2 mm in two anterior leads, or more than 1 mm in two inferior leads), or a newly developed left bundle branch block and elevated cardiac enzymes/biochemical markers, or a new Q-wave in two continuous leads on ECG. Non-ST-elevation myocardial infarction (NSTEMI) will be defined as chest pain lasting more than 10 minutes in combination with elevated cardiac troponin levels. Peri- and post-myocardial infarction will be defined as a myocardial infarction developing within 24 hours of PCI. This includes STEMI and NSTEMI with elevated biochemical markers more than three times normal level unit. A recurrent intervention is considered to be all unplanned revascularizations after the index procedure (CABG or PCI). All non-scheduled hospitalizations due to chest pain, arrhythmias not experienced previously, or congestive heart failure not experienced previously will be considered to be recurrent hospitalization for cardiac reasons. Stroke will be defined as all ischemic attacks resulting in neurological disorders, including transitory ischemic attack (TIA).

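### The NSTEMI outcome definition asks for no new marker rise, so further chest pain while the entry troponin is still raised can count as a new infarction

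*Protocol article*

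**What the plan says.** All references are to the protocol article.

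- **Outcome definition (Definitions).** For this study, "Non-ST-elevation myocardial infarction (NSTEMI) will be defined as chest pain lasting more than 10 minutes in combination with elevated cardiac troponin levels".
- **Entry criteria (Participants and recruitment).** Patients must have "ACS with ischemic symptoms (mainly chest pain) lasting over 10 minutes within the previous 72 hours", together with "ischemic ST-segment depression ≥ 1 mm and/or elevated troponin I, troponin T, or CK-MB". Symptoms are mandatory. The marker is one of two routes in, the other being ST depression.
- **Procedure-related infarction (Definitions).** "Peri- and post-myocardial infarction will be defined as a myocardial infarction developing within 24 hours of PCI". The next sentence sets the level: "This includes STEMI and NSTEMI with elevated biochemical markers more than three times normal level unit". No corresponding rule is given for CABG, although Intervention procedures names CABG as one of the two revascularization options.
- **Marker sampling (Definitions).** CK-MB and/or troponin "will be obtained at baseline, and if there are symptoms of myocardial ischemia".
- **Outcomes.** Myocardial infarction at 1 year, and death or myocardial infarction at 1 year, are secondary outcomes (Secondary outcome). The primary outcome is MACCE within 1 year (Primary outcome), and the article does not list its components. The Sample size section counts events from allocation.

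**The concern.** For a patient who enters on the troponin route, the test for an outcome NSTEMI is nearly the test already passed at entry. Follow-up begins during the index admission, when the entry troponin may still be raised. Another pain episode of more than 10 minutes in that period meets the definition whether or not new myocardium has been injured. The same can happen later in a patient with chronically raised troponin.

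The Definitions section asks for newness elsewhere. Bundle branch block and Q-waves must be new, and an arrhythmia or heart failure that leads to readmission must not have been experienced before. The infarction type that most resembles the entry diagnosis has no such condition.

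False infarctions could arise by different routes in the two arms: recurrent pain under medical treatment, and pain after a procedure under invasive treatment. At stake are the two secondary outcomes that use infarction and, if infarction is a MACCE component, the primary outcome as well.

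**Working it through.** **1. Entry and outcome side by side**

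| Element | Entry | Outcome NSTEMI |
|---|---|---|
| Symptom | Ischemic symptoms, mainly chest pain, over 10 min in the previous 72 h | Chest pain over 10 min |
| Marker | Elevated troponin or CK-MB, and/or ST depression | Elevated troponin |
| New rise over an earlier value | Not applicable | Not required |

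The two coincide for patients who enter with chest pain and raised troponin. They do not coincide for patients who enter on ST depression alone.

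**2. After a procedure.** Within 24 hours of PCI the threshold is more than three times normal. It refers to the normal level and not to the patient's own value before PCI. A patient already above it before PCI who then has pain can qualify with no further rise. After CABG only the general definition is available.

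**3. The plan's own sample size.** Inputs from Sample size: 40% versus 20%, 80% power, α 0.05 (taken as two-sided), 82 per group, raised to 100 for dropout. With p̄ = 0.30:

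n = [1.960·√(2·0.30·0.70) + 0.842·√(0.40·0.60 + 0.20·0.80)]² / 0.20² = (1.270 + 0.532)² / 0.04 = 81.2, rounded up to 82.

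The stated figure is reproduced. Power is 80.4% at 82 per arm and 87.6% at 100 per arm. The sample size arithmetic is not in question.

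**4. Sensitivity: equal mislabelling.** The documents give no false-infarction rate. Assume that infarction is part of MACCE and that a share f of otherwise event-free patients in each arm is labelled as having one. The observed rates become 0.40 + 0.60f and 0.20 + 0.80f, and the difference becomes 0.20(1 − f).

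| f (assumed) | Observed rates | Needed per arm | Power, 82 per arm | Power, 100 per arm |
|---|---|---|---|---|
| 0% | 40% vs 20% | 82 | 80.4% | 87.6% |
| 5% | 43% vs 24% | 96 | 73.6% | 81.7% |
| 10% | 46% vs 28% | 112 | 66.8% | 75.4% |
| 20% | 52% vs 36% | 150 | 54.2% | 62.7% |

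**5. Sensitivity: unequal mislabelling.** The true difference is 20 points.

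- 10% in the medical arm only: 0.40 + 0.60·0.10 = 46% versus 20%. The apparent difference is 26 points.
- 10% in the invasive arm only: 40% versus 0.20 + 0.80·0.10 = 28%. The apparent difference is 12 points, and power at 100 per arm is 43.2%.

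The sign of the bias depends on which arm has more false infarctions, and the documents do not say.

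**The case against.** Several points limit the concern, and they stand.

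- **The index event.** A reader might infer that the qualifying infarction itself is counted as an outcome. The documents do not support this. Qualifying symptoms and consent precede randomization, and the Sample size section counts events from allocation. What is missing is an explicit sentence of exclusion.
- **Any recurrent angina or post-procedure pain.** This reading is also too strong. The definition needs pain over 10 minutes and elevated troponin together, and within 24 hours of PCI the level must exceed three times normal. Exposure is mainly confined to the period when index troponin is still raised, or to patients with chronic elevation. Markers are redrawn only for symptoms, so silent rises after PCI are not sought.
- **A separate category for chest pain.** Readmission for pain is classified on its own: "All non-scheduled hospitalizations due to chest pain". This helps only in part. The categories are not said to be mutually exclusive, and pain during the index stay is not a new hospitalization.
- **A false finding in favour of invasive treatment.** Suppose the true rate is 30% in both arms, with 100 per arm, and 5, 10 or 15% of event-free patients are mislabelled in the medical arm only. The observed medical rates are then 33.5, 37 and 40.5%, and the chance of a spurious significant benefit is about 8, 18 or 34%, against 2.5%. These figures recompute, but they place every false infarction in one arm at assumed rates. At equal rates the chance stays near 2.5%, and the cost is power. The documents do not support a predicted direction.
- **MACCE.** Its components are not listed, so an effect on the primary outcome is a reasonable inference and not a stated fact.

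None of this supplies the missing requirement for a new rise.

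**Conclusion.** The point holds in a narrow form. The NSTEMI outcome is a fixed rule, stated in the article for this study, and it cannot separate new injury from troponin still raised after the entry event or chronically. The absolute threshold after PCI does not cure this for patients already above it, and CABG has no rule of its own.

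The effect on infarction, and on death or infarction, at 1 year is direct. The effect on MACCE rests on infarction being a component. Its size is unknown, because neither the false-infarction rate nor its split between arms is in the documents. Under the assumed equal rates of 5 to 20%, power at 100 per arm falls from about 88% to between 82% and 63%. Unequal rates bias the contrast, in a direction that cannot be predicted.

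One related matter is separate and minor. Entry accepts "ischemic symptoms (mainly chest pain) lasting over 10 minutes", whereas an outcome NSTEMI needs chest pain, so an event with other ischemic symptoms could be sampled and yet not counted as NSTEMI.

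**What to change.** Amend the Definitions section before the analysis:

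1. State that an outcome infarction must begin after randomization and that the qualifying index infarction is not an outcome.
2. Where the last available marker value is already elevated, require a new rise over that value. The sponsor should prespecify the size of the rise, since the documents give no basis for a figure.
3. Apply the same relative rule to PCI-related and CABG-related infarction wherever a pre-procedure value exists.

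The change is mainly one of wording, because baseline and symptom-driven values are already collected. It still has costs. Some recorded infarctions must be re-classified, and fewer events may be counted. The article schedules no routine sample before PCI or CABG, so making a pre-procedure comparison mandatory would need extra sampling; item 3 is therefore limited to cases where a value exists. Where the only earlier value is a single early baseline sample, a later rise may still belong to the index infarction, so the fix reduces the problem without removing it.

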### Outcome and safety measurements

There are several secondary outcome measures for this trial. The definitions of some of the outcome measures are. Firstly, the grade of angina pectoris as determined by the patient’s perception of angina pectoris according to the Seattle Angina Questionnaire (SAQ) [8]. This assessment will be optional for the patient. Secondly, the patient’s perception of quality of life according to SF-36 [9]. This assessment will also be optional for the patient. Thirdly, the physician’s perception of frailty at enrollment, according to the Canadian Study of Health and Aging (CSHA) Clinical Frailty Scale [10]. Fourthly, major bleeding, defined as either intracranial bleeding, a decrease in hemoglobin level of more than 50 g/L, or bleeding requiring surgery. Fifthly, minor bleeding, defined as a decrease in hemoglobin level of more than 30 g/L (but less than 50 g/L), spontaneous gross hematuria, hematemesis, hematoma, or pseudoaneurysm requiring treatment (other than surgery). A timeline of the interventions and measurements is shown in Table 1.

**Table 1 Tab1:** **Schedule of enrollment, interventions, assessments, and outcome/safety measures for the octogenarian study**

	STUDY PERIOD						
	Enrollment	allocation	Post-allocation				Close-out
**Time point****		**0**	**day 1**	**in-hospital**	**at discharge**	**day 30**	**1 year**

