### Secondary outcome

Secondary outcome measures include: any MACCE within 1 month, death at 1 year, any myocardial infarction at 1 year, death or myocardial infarction at 1 year, major bleeding at 30 days, and minor bleeding at 30 days.

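### The bleeding definitions leave a hemoglobin fall of exactly 50 g/L unclassified, do not name fatal bleeding as major, and do not make minor exclusive of major

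*Protocol article*

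**What the plan says.** The Protocol article defines the two bleeding classes under Outcome and safety measurements. The upper class is "major bleeding, defined as either intracranial bleeding, a decrease in hemoglobin level of more than 50 g/L, or bleeding requiring surgery". The lower class has a hemoglobin limb and a clinical limb. It begins "minor bleeding, defined as a decrease in hemoglobin level of more than 30 g/L (but less than 50 g/L), spontaneous gross hematuria, hematemesis"; the clinical limb in full consists of "spontaneous gross hematuria, hematemesis, hematoma, or pseudoaneurysm requiring treatment (other than surgery".

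The section Secondary outcome uses both classes as listed outcomes: "major bleeding at 30 days, and minor bleeding at 30 days". Table 1 labels bleeding as the safety measure.

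On measurement, the section Definitions says "Blood samples for hemoglobin will be obtained at baseline, and if there is suspicion of bleeding". The same section says "All-cause mortality will be analyzed for this study". Reporting of adverse events counts death and life-threatening events among the serious adverse events. Fatal bleeding is not named in either bleeding class, and transfusion is not mentioned anywhere in the article.

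**The concern.** A two-class severity scale should put every qualifying event in one class and only one, and a worse event should never land in a lower class than a milder one. These definitions fail on three counts: a value between the classes belongs to neither, a fatal bleed can rank below a non-fatal one, and a single bleed can meet both definitions.

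At stake are two of the six listed secondary outcomes, in a trial that names fear of procedural complications as a reason for withholding invasive treatment and hypothesizes that harm will be acceptable. With 100 patients per arm, bleeding counts may be small, so the class given to single events can be visible in the result.

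**Working it through.** The article gives no bleeding rate and calculates nothing for bleeding, so there is no figure of its own to reproduce on this point. Its one calculated figure, 82 per group under Sample size, concerns MACCE and does not use the bleeding classes. The check is to apply the definitions literally.

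**Rules as written** (d = fall in hemoglobin, g/L)
- Major: intracranial, or d > 50, or surgery required.
- Minor: 30 < d < 50, or a listed clinical sign.

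**Results**

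| Case | Meets major | Meets minor | Class |
|---|---|---|---|
| d = 49, no sign | no | yes | minor |
| d = 50, no sign | no | no | none |
| d = 50, hematemesis | no | yes | minor |
| d = 51, no sign | yes | no | major |
| d = 60, hematemesis | yes | yes | both |
| Fatal hematemesis, no later hemoglobin value, no surgery | no | yes | minor |
| Fatal retroperitoneal bleed, no later value, no surgery, no listed sign | no | no | none |
| Fatal bleed with d > 50 or surgery | yes | – | major |

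Three points follow.

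1. *Boundary.* A bleed 1 g/L worse than one classed as minor drops out, and at 1 g/L more it returns as major. A fall of exactly 30 g/L is also unclassified, but that is only the lower limit of the scale and not a gap.
2. *Fatal bleeding.* The fatal cases in the table can arise under the article's own sampling rule. After baseline, hemoglobin is taken only when bleeding is suspected, so a patient may die with no later value, or with one taken before the fall has shown. If the words on treatment in the minor definition apply to every listed sign and not only the last, an untreated fatal hematemesis is in neither class. On either reading it is not major.
3. *Overlap.* Nothing says that a bleed meeting major is removed from minor, so the d = 60 case can enter both 30-day outcomes.

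**Size**
- One reclassified event in an arm of 100: 1/100 = 1 percentage point, whatever the underlying rate.
- Illustration only, assuming 5% major bleeding in each arm: 5 events per arm, so one event is 1/5 = 20% of the count. The 95% half-width for the difference is 1.96 × √(2 × 0.05 × 0.95 / 100) = 0.060, or about 6 points. One or two such events (1 to 2 points) lie well inside that.

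The article gives neither a bleeding rate nor a distribution of hemoglobin falls, so the expected number of affected events cannot be calculated.

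**The case against.** The strongest reply is that the definitions work for most serious bleeds and that nothing fatal is lost to the trial. Any bleed with a fall above 50 g/L, at an intracranial site or requiring surgery is major. The gap at 50 concerns one value, and only when no listed sign is present. Every death counts in all-cause mortality and in death at 1 year, and a fatal bleed associated with the study agents or the intervention is a serious adverse event. All of this stands and limits the point. It does not remove it: neither mortality nor adverse-event reporting puts a fatal bleed into the major bleeding count, which is a listed outcome. Nor is this a detail left to a fuller document, because the article states the rules in full and they misclassify if followed.

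A reader might infer more than the article supports:

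- *That hematemesis is minor however severe.* It is not: with a fall above 50 g/L or surgery it meets a major criterion.
- *That the errors flatter the invasive arm.* The same definitions apply to both arms, antiplatelet treatment is recommended in both, the typical access-site events (hematoma, pseudoaneurysm) are listed signs, and no bleeding rate by arm is given. The direction cannot be established.
- *That ignoring transfusion is an error.* Transfusion can mask a fall, but only if the relevant sample was taken afterwards. Sampling on suspicion of bleeding is just as consistent with a value taken before. Any correction factor would be an assumption, and applying one would need retrospective data in a trial recruiting since October 2009. This is an optional design choice, as is a class for other overt bleeding.
- *That bleeding alone carries the safety hypothesis.* The hypothesis concerns adverse events, which the article defines and schedules separately.

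**Conclusion.** The point holds in a limited form. The gap at exactly 50 g/L and the missing exclusivity are faults in the stated rules. The absence of fatal bleeding from a closed major list is a weakness of definition with a clear consequence: a fatal bleed outside the skull, without surgery or a recorded fall above 50 g/L, is counted as minor or not at all in the 30-day bleeding outcomes. This affects some severe bleeds, not severe bleeds in general.

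The effect is probably small: 1 percentage point per event in an arm of 100, with the number of events unknown. The conclusion rests on reading the definitions literally and assumes that hemoglobin falls can take the value 50 g/L as recorded. The primary endpoint and the sample size are unaffected.

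**What to change.** Reword the two definitions under Outcome and safety measurements:

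- **Major:** fatal bleeding, intracranial bleeding, bleeding requiring surgery, or a hemoglobin fall of at least 50 g/L.
- **Minor:** bleeding that does not meet major, with a fall of more than 30 and less than 50 g/L or one of the signs already listed.

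Apply the revised wording in the same way to all events in both arms, including those already recorded. Because the trial is open-label, this is best settled before bleeding is compared between arms.

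The change is to wording and needs no new measurement, but events already classified must be read again against the new text. The downside is that the major bleeding count may be slightly higher. If the sponsor also wishes to account for transfusion or add other overt bleeding, that is a separate choice with its own data cost and is not needed to close the gaps described here.
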